#### Quality control

Necessary measures as per the National guidelines for data quality in surveys [62] such as data collection by trained researchers, validation and pilot-testing of study instruments prior to use, meticulous checking and standardization of equipment, and reagents to be used, etc. will be taken to maintain data quality at the highest possible level.

#### Data management and analysis

All participants’ data will be coded by assigning unique identifiers. These codes will be used to identify and link various parameters of the individual participants. Data from the filled questionnaires/clinical proforma as well as the laboratory analysis values will be entered into the latest version of Microsoft Excel spreadsheets. Statistician of the team will supervise data entry and to ensure error-free data at least 10% of the entered data will be randomly verified.

Once data entry is complete, hard copies of questionnaire/proforma will be stored in a secure archive in the institute. Similarly, all entered data will be stored in password protected computer systems with access restricted to the research team alone. The data collected/generated in this study will be stored for a period of ten years. The primary investigator will be in-charge of data safety and back-up maintenance. Anonymized data set will be shared publicly during publication of study results.

All statistical analyses will be performed using IBM SPSS Statistics (version 25). For ordinal and continuous variables, the values will be given as descriptive statistics (like mean, median, standard deviation, 95% confidence interval, interquartile range); and categorical variables will be given as numbers (percentages) and proportions. Association for different health aspects with pollution level of various parameters of air/water will be made using Pearson’s chi-square test for independent categorical data. By considering the variability within and between groups; t-test and ANOVA will be used to analyze the mean differences between two and more groups respectively for various anthropological parameters, the concentration of air/water pollutants, etc. The Mann–Whitney U test and Wilcoxon signed ranks test will be used for independent and dependent for ordinal and continuous data with respect to different health aspects. Pearson and Spearman’s correlation coefficient will be used to examine the association between different variables. Multiple linear and logistic regression models will be used to estimate the relationship for different neurological assessments with a set of the independent variable. For all statistical tests, two-sided P-values <0.05 will be considered to be significant.

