The industrial area of Birlagram Nagda in the central Indian state of Madhya Pradesh (MP), has been under scrutiny due to the pollution emanating from the multiple viscose rayon textile and associated chemical manufacturing industries operating in the area [15]. As per data compiled by the Central Pollution Control Board (CPCB) [16] in 2013, the apex government run agency monitoring environmental pollutant concentrations in the country, the area has a comprehensive environment pollution index score of 66.67, which indicates that it is among the “severely polluted” industrial clusters in India. Although recent statistics have shown improvement in the area’s pollution index, it is still listed in the top hundred polluted industrial clusters in India [17]. Major chemical pollution associated with viscose rayon textile manufacturing occur secondary to gaseous emission of carbon disulphide (CS_2_), Hydrogen Disulphide (H_2_S), Hydrogen Chloride (HCl), Chlorine (Cl_2_), Sulphur oxides (SO_2_ and SO_3_) and untreated discharge of viscose fibre wastewater effluent containing high concentration of heavy metals, and other toxic substances into natural water sources [9]. However, there is hardly any scientific evidence regarding the health effects of residing near the industries of Birlagram. Considering the growing health concerns of the local public, regulatory authorities in India directed the industries operational in the region to implement pollution control strategies as well as commissioned detailed environmental and health-oriented investigation of the issue [18]. The current study was initiated as per directions of the local authorities to evaluate the health effects of exposure to multiple pollutants emitted from the industrial activity in Birlagram. Specifically, the objectives of the current study include:

To measure the concentration of gaseous pollutants (i.e. CS_2_, H_2_S, HCl, Cl_2_, and SO_2_) in the ambient air in the study area.To measure the concentrations of heavy metals and anions [i.e. lead (Pb), mercury(Hg), aluminium (Al), chloride (Cl^-^) and sulphate(SO_4_^2-^)] in groundwater samples.To determine the association between the concentration levels of pollutants in air and water samples with that in bio-samples (blood and urine).To identify the association between exposure to pollutants and health effects in study participants.

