#### Sampling strategy

In this study stratified random sampling technique will be used for selection of participants where stratification will be done based on environmental factors that are likely to affect exposure. Since both distance from fixed contamination source as well as local environment features such as meteorology, topography, etc. are the major factors affecting the dispersion of both ambient air as well as water pollutants [26], a map of the study area was created to assist in selection of exposure monitoring locations and in participant sampling (see Fig 3). Briefly, taking Birlagram industrial region as the centre, villages located within consecutive circles of radius 2 kilometres (km), 5km and 10km were demarcated on the map using ArcInfo (version 10). This strategy was used as it is expected that gaseous pollutants’ dispersion occurs homogenously in all directions independent of anthropogenic roadways and that with increase in distance the pollutant concentration will become diluted enough to prevent adverse health effects [27]. Based on seasonal wind pattern data retrieved from local authorities, the north-eastern quadrant of the circular study area was seen to be the downwind area for most of the year. The downstream direction of River Chambal falls in the north-western quadrant of the circular study area. Therefore the majority of the pollutants are expected to disperse in the northern direction increasing the potential risk faced by the residents and so, we decided to over-represent the northern hemisphere.

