**Fig 3 pone.0264154.g003:**
[figure not shown]
Map of the study area created by research team to assist in selection of exposure monitoring locations and in participant sampling. [Note: The inset in the map shows the Ujjain district of the central Indian province of MP. Within the Khachrod Tehsil of the Ujjain district, lies the study area of the current project. Considering the Birlagram industrial region as the centre, three concentric circular regions were demarcated based on distance (2, 5 and 10 km from the centre)].

Finally, 2000 participants will be selected from the villages in the northern hemisphere while 1003 will be taken from the villages in the southern hemisphere within the 10km radius comprising a total of 3003 participants. In each hemisphere, a fixed number of villages will be selected randomly from those situated in each of the 0-2km, 2-5km and 5-10km zones. Further in each selected village, using the list of all individuals residing in the villages that will be retrieved from the local authorities as the sampling frame, individuals meeting the eligibility criteria will be randomly invited for participation in the study. Total number of individuals sampled in each village will be proportionate to the total population of the selected village.

Participants will be selected for the study only if they fulfill all the following criteria:

Adults (≥18 years of age) of both genders (except pregnant women),Should have been residing for at least one year in the selected village,No history of neuropsychiatric conditions that might hinder completion of neurobehavioral tests,No history of other conditions that are contraindications for performing Pulmonary function test (PFT) like presence of any active disease (e.g. pulmonary Tuberculosis, active haemoptysis, orofacial pain, acute respiratory infection including COVID-19 i.e. coronavirus disease caused by SARS-Cov-2 virus) or recent history (within previous 1 month) of myocardial infarction/aneurysm/surgery, etc.

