Industrial pollution is a multidimensional issue since it occurs in multiple environmental matrices and in turn affects multiple organ systems in the human. Therefore, in our study we will focus on multiple objectives with an overarching goal to assess the potential health effects of exposure. A major strength of this study is therefore its multidisciplinary research team with expertise of investigators ranging from health sciences like epidemiology and neurology to environmental sciences and basic science. To strengthen the association between pollutant concentration in environmental matrices and health effects, human exposure assessment will be done in a subset of the population to ascertain dose-response relation. Therefore, exposure to CS_2_ will be confirmed using the urine azide test which has been reported to adequately reflect occupational CS_2_ inhalation by published literature [34–36]. Furthermore, blood levels of heavy metals will also be determined to estimate exposure of villagers to toxic metals, viz. Pb, Al and Hg from various environmental matrices, viz. air, water and food/soil. However, pertaining to resource limitation, biomonitoring will be conducted in a subset of the total study population.

The current study also faces certain limitations. Long term follow-up of the participants to establish a temporal relationship between exposure and outcome is not possible in our cross-sectional study. Considering the ongoing dispute between local residents, viscose rayon manufacturers and the local authorities, the current study prioritised timely delivery of baseline health effect information. Future research might therefore focus on longitudinal data collection on the environmental health effects of viscose rayon manufacturing. Furthermore, past exposure assessment will be done through questionnaire data and is therefore, prone to recall bias. Although data will be collected for multiple relevant confounders including other environmental/meteorological, socioeconomic and diet/lifestyle factors, the risk of residual confounding cannot be completely eliminated.

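### Non-neurological binary outcomes are tied to pollution level only by Pearson's chi-square, which ignores the order of exposure; a trend test or logistic slope would suit the expected gradient better, at little cost

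*Protocol article*

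**What the plan says.** The Data management and analysis section of the protocol article links health outcomes to environmental measurements in one sentence: "Association for different health aspects with pollution level of various parameters of air/water will be made using Pearson’s chi-square test for independent categorical data". Two other sentences there name methods that can use order. One is general: "Pearson and Spearman’s correlation coefficient will be used to examine the association between different variables". The other is confined to one outcome domain: "Multiple linear and logistic regression models will be used to estimate the relationship for different neurological assessments". The threshold throughout is "For all statistical tests, two-sided P-values <0.05 will be considered to be significant".

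The objective being served, in the Introduction, is "To identify the association between exposure to pollutants and health effects in study participants". The Sampling strategy gives a reason to expect a graded effect: "with increase in distance the pollutant concentration will become diluted enough to prevent adverse health effects". Villages are drawn from those "situated in each of the 0-2km, 2-5km and 5-10km zones". Under Environmental monitoring of pollutants at study sites, gases are logged over 24 hours and metals are reported in ppb, so exposure is recorded as a quantity. The article does not say how, or into how many categories, pollutant levels would be grouped.

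**The concern.** Pearson's chi-square tests whether at least one exposure group differs from the others. It needs the concentration turned into categories, and it gives the same answer if those categories are shuffled. The effect the study expects is a gradient: more pollutant nearer the source, more ill-health. For the non-neurological binary outcomes, including the ECG abnormality that determined the sample size, it is the only test expressly tied to pollution level.

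Two things are at stake. With three or more groups, power is spread over directions that do not correspond to a gradient. And a significant result does not by itself show that illness rises with pollutant level, because a pattern with the middle group worst can be significant too.

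**Working it through.** **Inputs from the article.** p = 0.26, z = 1.96, non-response R = 0.30, design effect 1.25, margin d = 0.02 and n = 3003 (Sample size calculation); two-sided 5% level (Data management and analysis); three distance zones (Sampling strategy). No power is stated for any association test.

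**The plan's own figure.** n = 1.96² × 0.26 × 0.74 × 1.30 × 1.25 / 0.02² = 3002.7, which rounds to 3003. It reproduces. It is a precision calculation for one proportion and says nothing about power for exposure–outcome tests.

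**Assumptions.** Number of groups k (not stated, so varied), equal group sizes, a linear gradient, independent participants.

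**Step 1: cost of ignoring order.** For a linear gradient over k equal groups, both tests have the same noncentrality, λ = (N/k) Σ(pᵢ − p̄)² / [p̄(1 − p̄)]. The trend test spends 1 degree of freedom and chi-square spends k − 1. A trend test with 80% power has λ = (1.960 + 0.842)² = 7.85. Chi-square power is then the probability that a noncentral chi-square on k − 1 df with λ = 7.85 exceeds its 5% critical value. The last column is the largest loss over all gradient sizes.

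| k | Critical value | Chi-square power | Loss with trend test at 80% | Largest loss |
|---|---|---|---|---|
| 2 | 3.84 | 80.0% | 0 | 0 |
| 3 | 5.99 | 70.9% | 9.1 | 10.5 |
| 4 | 7.81 | 64.5% | 15.5 | 17.0 |
| 5 | 9.49 | 59.5% | 20.5 | 21.8 |

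**Step 2: an example at the study's size.** N = 3003, average 26%, 5-point difference from lowest to highest of three groups: λ = 1001 × 2 × 0.025² / (0.26 × 0.74) = 6.50. Power is 72.2% for the trend test and 62.1% for chi-square. At N = 3003/1.3 = 2310, the figures are 60.9% and 50.4%. With an 8-point gradient and N = 3003, they are 98.3% and 96.3%, so the loss shrinks when the effect is large.

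**Step 3: cost of cutting the concentration.** Suppose each person had an individual, normally distributed (log) concentration and the slope test had 80% power. Equal grouping keeps 0.637, 0.793, 0.861 and 0.897 of the information for k = 2 to 5. A trend test on the groups then has 60.9%, 70.4%, 73.9% and 75.6% power, and chi-square has 60.9%, 60.1%, 57.3% and 54.3%. The 19-point loss at k = 2 comes entirely from the cutting. This is an upper illustration, because air is monitored at sites (one representative site per cluster) and groundwater by village, so participants share values.

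**Step 4: non-monotone pattern.** Three groups of 1001, average 26%, middle group 5 points higher: the deviations are −1.67, +3.33 and −1.67 points, so λ = 1001 × 0.001667 / 0.1924 = 8.67. Chi-square on 2 df is significant 75% of the time. The linear trend is zero, so the trend test rejects at its nominal 5%.

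**The case against.** **Order-using methods are already listed.** Correlating a 0/1 outcome with a scored exposure is essentially a linear-by-linear trend test, and logistic regression is in the plan. The t-test and Mann–Whitney sentences could also be read as comparing concentrations between people with and without an abnormality. A reader should therefore not infer that the plan contains no method able to detect a gradient. What stands against this is that none of those sentences names non-neurological binary outcomes against pollution level, whereas the chi-square sentence names health outcomes against pollution level directly.

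**The objective asks only for association.** This is right. A reader might infer that chi-square contradicts a stated dose-response aim, but the Discussion sentence, "human exposure assessment will be done in a subset of the population to ascertain dose-response relation", concerns biomonitoring in a subset, not the air and water comparison. An omnibus test is a legitimate test of association. The case for a graded alternative rests on the Sampling strategy.

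**The gradient need not be linear.** The dilution sentence can be read as a threshold, and exposure also depends on wind and river direction. If only the highest of three equal groups differs and an equally spaced trend test has 80% power, chi-square has 83% (87% with four groups, 91% with five). This stands: neither test is uniformly better.

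**Direction would be visible.** Categorical variables are to be reported as numbers and percentages, so a hump need not be mistaken for a gradient. That softens the interpretive risk but does not give a test of the gradient.

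**Grouping detail may sit in a document not shown.** The missing number of categories is therefore not itself a finding. It only means the loss must be given as a range.

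**Conclusion.** The point holds as a modest one. For ECG abnormality, hypertension and impaired lung function, the only test explicitly tied to air or water pollution level ignores the order of exposure that the design expects to matter.

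For a linear gradient, ignoring order costs nothing with two groups and, with the same-groups trend test at 80% power, about 9, 16 and 20 points with three, four and five (at most 10.5, 17.0 and 21.8). Three is the only ordered exposure grouping the article describes, so roughly 10 points is the figure most relevant here. Cutting the concentration adds a further loss only so far as exposure is nearly continuous, which site- and village-level measurement limits.

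A reader might infer a general loss of 20 points or more. The article does not support that: ignoring order costs that much only with five or more groups, and the larger figures at two or three groups need individual continuous exposure.

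All figures assume independent participants. Shared exposure within villages would lower the absolute power of both tests. Chi-square is not invalid here; it is less well aimed.

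**What to change.** Replace the chi-square sentence in Data management and analysis. For binary health outcomes, test association with each pollutant by the slope in a logistic model on the measured (log) concentration. Where only ordered zones are available, use a Cochran–Armitage or linear-by-linear trend test with stated zone scores, such as distance. Report the odds ratio with its confidence interval and direction, for example per doubling of concentration. Keep Pearson's chi-square for unordered factors and as a secondary check for departure from trend.

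The cost is one sentence. SPSS, already the chosen package, provides both analyses, and no extra data are needed. The downside is that a trend test is somewhat less sensitive to threshold or non-monotone patterns, which the secondary chi-square covers. Allowance for shared exposure within villages is a separate matter that arises with either test.

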### Participant selection and sampling strategy

#### Sample size calculation

As the health effects of residing near textile manufacturing industries in Birlagram, India are not previously documented, we calculated the sample size using the statistics reported by a previous study conducted in Taiwan where authors [24] found that 26.3% of the population exposed to emissions from a viscose rayon manufacturing industry had electrocardiogram (ECG) abnormalities. Since one of our outcomes is the identification of the proportion of exposed population in Birlagram, India with ECG abnormalities, we calculated sample size as follows:

$$\text{Sample}\;\text{size}\;\left(\text{n}\right)=\frac{{\text{z}}^{2}\text{pq}*\left(1+\text{R}\right)*\text{Deff}}{{\text{d}}^{2}}$$

Where, p = Expected population proportion = 0.26; q = 1-p = 0.74; z = z value for 5% level of significance is 1.96; R = Non-response rate (assumed to be 30% as pooled non-response rate reported by a systematic review of participation response in Indian industrial surveys [25]); Deff = Design effect(1.25 for systematic sampling); and d = Margin of error 2% (assumed to be 0.02). The calculated sample size was 3003.

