#### Environmental monitoring of pollutants at study sites

Pollutants for assessment in both environmental and human matrices were selected based upon their relevance to viscose rayon and associated chemical manufacturing industry identified through review of previously published literature [9].

*i) Monitoring of gaseous pollutants in ambient air*. The ambient air monitoring will be carried out in the study area (see Fig 2) for identified gaseous pollutants viz., CS_2_, H_2_S, HCl, Cl_2_, and SO_2_ using a factory calibrated, electrochemical sensor based multi-gas monitor (Make: Swan**®** Environmental Pvt. Ltd. India, Model: GRI-IAT; Sensor make: Membrapor**®**, Switzerland). The monitoring will be carried out in post-monsoon season (October-January). The instrument has an inbuilt geographical positioning system to record the coordinates of sampling site. The ambient air monitoring will be carried out continuously for 24 hours in at identified sites. In case of cluster of sites, a representative site will be identified for gaseous monitoring. The monitor will be placed at more than 3 metres height from ground level at a place having uninterrupted power supply. The data loggers present in the instrument will store the data at set frequency and will be utilized for further statistical analysis. The sampling and monitoring of ambient air for said pollutants will be carried out following the existing guidelines of CPCB, Ministry of Environment, Forests and Climate Change, New Delhi, India [28].

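### Health outcomes are to be tested against village- or site-level air and water pollution with methods that ignore the two-stage village sampling, so P-values will be too small by an amount that depends on the unstated village count and intraclass correlation

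*Protocol article*

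**What the plan says.** **Sampling.** Under Sampling strategy, in each hemisphere "a fixed number of villages will be selected randomly from those situated in each of the 0-2km, 2-5km and 5-10km zones". Individuals are then drawn at random from each selected village's list of residents, in numbers proportionate to village population. The north receives 2000 participants and the south 1003. The total number of villages is not given.

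**Exposure measurement.** Air is monitored for 24 hours at identified sites, and the section on ambient air adds: "In case of cluster of sites, a representative site will be identified for gaseous monitoring". Groundwater comes from all accessible sources in 10 downstream villages. Individual exposure is measured separately: blood metals in every tenth participant, and a urine iodine-azide test that the Abstract and Discussion place in a subset.

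**Analysis.** The Data management and analysis section states: "Association for different health aspects with pollution level of various parameters of air/water will be made using" Pearson's "chi-square test for independent categorical data". It also names t-test, ANOVA, Mann–Whitney, Wilcoxon signed ranks, Pearson and Spearman correlation, and multiple linear and logistic regression. It closes with: "For all statistical tests, two-sided P-values <0.05 will be considered to be significant". No village effect, cluster-robust variance or survey-design analysis is named.

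**Sample size.** The Sample size calculation includes a design effect of 1.25, attributed to systematic sampling. No stated analysis carries it forward.

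**The concern.** People in one village share water, housing, occupation, diet and examination conditions as well as pollution, so their outcomes tend to be alike. When the exposure also varies mainly between villages or sites, the evidence on it comes largely from the number of villages and much less from the number of people. A chi-square test on individuals counts each person as a separate piece of evidence.

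The fourth objective (exposure and health effects) is most affected. The environment-to-biosample part of the third objective is affected to a lesser degree. The Discussion places the study within an ongoing dispute between residents, manufacturers and authorities. A chance difference between a handful of villages could then be reported as a pollution effect.

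The article also sits uneasily with itself: it allows for a design effect above 1 when sizing the study, then names tests that imply a design effect of exactly 1.

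**Working it through.** **1. The plan's own figure.** Inputs from the Sample size calculation: "p = Expected population proportion = 0.26", q = 0.74, "z = z value for 5% level of significance is 1.96", R = 0.30, Deff = 1.25, d = 0.02.

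n = 1.96² × 0.26 × 0.74 × 1.30 × 1.25 / 0.02² = 3002.69, which rounds up to the stated 3003.

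**2. Formulas.** For an exposure constant within villages of equal sample size m:

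- Deff = 1 + (m − 1) × ICC
- true standard error / naive standard error = √Deff
- actual two-sided type I error of a nominal 5% test = 2 × [1 − Φ(1.96/√Deff)]

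**3. The protocol's own design effect.** If 1.25 were the true inflation, √1.25 = 1.12 and the type I error is 2 × [1 − Φ(1.753)] = 8.0%. Village clustering stays within 1.25 only if ICC ≤ 0.25/(m − 1). That is 0.0010 for 12 villages (m = 250.25) and 0.0025 for 30 villages (m = 100.1).

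**4. All 3003 participants.** Neither the village count nor the ICC is in the document. *Assumed:* 12 to 30 villages, that is 2 to 5 in each of the 6 hemisphere-by-zone strata, and ICC 0.005 to 0.05.

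| ICC | Deff, 12 villages | Type I error | Deff, 30 villages | Type I error |
|---|---|---|---|---|
| 0.005 | 2.25 | 19.1% | 1.50 | 10.9% |
| 0.01 | 3.49 | 29.4% | 1.99 | 16.5% |
| 0.05 | 13.46 | 59.3% | 5.96 | 42.2% |

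Outside that range, at ICC 0.01, 10 villages give 33% and 60 villages give 11%. If only 3003/1.3 = 2310 people take part, 30 villages at ICC 0.01 give 14%.

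**5. Simulation check.** Beta-binomial outcome with mean 0.26, village-level binary exposure, Pearson chi-square on individuals, 4000 runs per setting. At ICC 0.01 the rejection rate was 33.6%, 20.5% and 16.8% for 10, 20 and 30 villages; the formula gives 32.7%, 21.4% and 16.5%. At ICC 0 it was 4.5–4.7%, so the excess comes from the clustering.

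**6. Blood metals.** Every tenth participant is about 300 people, so m = 25 (12 villages) or 10 (30 villages).

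| ICC | Deff, 12 villages | Type I error | Deff, 30 villages | Type I error |
|---|---|---|---|---|
| 0.005 | 1.12 | 6.4% | 1.045 | 5.5% |
| 0.01 | 1.24 | 7.8% | 1.09 | 6.0% |
| 0.05 | 2.20 | 18.6% | 1.45 | 10.4% |

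The size of the iodine-azide subset is not given, so no figure is offered for it.

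**7. Groundwater.** The article gives 10 villages. A two-group comparison of village means then has 10 − 2 = 8 degrees of freedom, so the normal reference distribution is itself too generous, apart from the design effect.

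**The case against.** *The exposure assignment is inferred.* This stands as a caveat. Several wells per village would allow water values to be assigned by source, and the formula would then overstate the inflation. For air, the monitoring described offers no evident finer unit than the site.

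*Not every named method assumes independent people.* This also stands. The Wilcoxon signed ranks test is for dependent data, though it does not deal with villages. The t-test and ANOVA are partly meant for pollutant concentrations, where the unit is an environmental sample. The regressions are named without a variance estimator, and a fuller plan may exist. The chi-square sentence is the firm ground: it ties air and water level to health outcomes and specifies independent data.

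*The size is assumed.* A reader might infer that all P-values for the third and fourth objectives will be far too small. The document does not support that, because it gives neither the ICC nor the total village count. The inflation could be as low as 8% at the protocol's own design effect. The figures for 3003 people do not carry over to a subset of about 300. Biomarker ICCs might be higher than assumed here, but nothing in the article says so. Where urine or blood measures serve as the exposure, they vary within villages and the inflation is smaller.

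*This is detail for an analysis plan.* This does not stand. The article names a test whose assumption conflicts with the sampling it describes.

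**Conclusion.** The point holds for inference on air and water level against health outcomes and, more mildly, on environmental level against biomarkers. The direction is certain for any positive ICC when the exposure is shared within villages. The size is conditional: from 8% if 1.25 is the true design effect, to 42–59% at ICC 0.05 with 12 to 30 villages. The blood-metal analyses lie between about 6% and 19% over the same assumptions.

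All these figures assume equal village sizes and exposure that is constant within villages. Sampling in proportion to population will make sizes unequal, which generally raises the design effect; exposure assigned by individual well would lower it. The stated analysis should be changed before the data are analysed.

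**What to change.** Amend the Data management and analysis section as follows.

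- For air or water exposure against health outcomes, and for environmental level against biomarker, replace the independent-observation tests with linear or logistic mixed models with a random village intercept, or GEE clustered on village. Where one monitoring site serves several villages, cluster on the site.
- Use small-sample degrees of freedom based on the number of clusters (10 villages for groundwater).
- Account for hemisphere and distance zone, which are the sampling strata, and for the over-representation of the north. Do this without adjusting away the exposure contrast, since distance and direction are themselves proxies for exposure.
- State the rule that links each participant to an air and a water value, and the number of villages.
- Keep chi-square, t-test, ANOVA and simple correlations for description.

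No new data are needed, but the change costs precision. At ICC 0.01, 3003 people in 12 villages are worth about 3003/3.49 = 860 independent ones for a village-level exposure; at ICC 0.05 they are worth 3003/13.46 = 223. The report should state the wider intervals and lower power. Recovering that power would take more villages, which is a design change and not part of this fix.
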